# A Design to Investigate the Feasibility and Effects of Partnered Ballroom Dancing on People With Parkinson Disease: Randomized Controlled Trial Protocol

**DOI:** 10.2196/resprot.3184

**Published:** 2014-07-22

**Keywords:** Parkinson disease, ballroom dancing, balance, posture

## Abstract

**Background:**

Self-help and physical leisure activities has become increasingly important in the maintenance of safe and functional mobility among an increasingly elderly population. Preventing the cycle of deterioration, falling, inactivity, dependency, and secondary complications in people with Parkinson disease (PD) is a priority. Research has shown that people with PD are interested in dance and although the few existing trials are small, initial proof of principle trials from the United States have demonstrated beneficial effects on balance control, gait, and activity levels. To our knowledge, there has been no research into long-term effects, cost effectiveness, the influence on spinal posture and turning, or the personal insights of dance participants.

**Objective:**

The purpose of this study was to determine the methodological feasibility of conducting a definitive phase III trial to evaluate the benefits of dance in people with PD. We will build on the proof of principle trials by addressing gaps in knowledge, focusing on areas of greatest methodological uncertainty; the choice of dances and intensity of the program; for the main trial, the availability of partners, the suitability of the currently envisaged primary outcomes, balance and spinal posture; and the key costs of delivering and participating in a dance program to inform economic evaluation.

**Methods:**

Fifty participants (mild-to-moderate condition) will be randomized to the control (usual care) or experimental (dance plus usual care) groups at a ratio of 15:35. Dance will be taught by professional teachers in a dance center in the South of England. Each participant in the experimental group will dance with his or her spouse, a friend, or a partner from a bank of volunteers. A blinded assessor will complete clinical measures and self-reported ability at baseline, and at 3 and 6 months after randomization. A qualitative study of a subgroup of participants and partners will examine user’s views about the appropriateness and acceptability of the intervention, assessment protocol, and general trial procedures. Procedures for an economic evaluation of dance for health care will be developed for the main trial.

**Results:**

Recruitment began in January 2013 and the last participant is expected to complete the trial follow-up in June 2014.

**Conclusions:**

Findings from our study may provide novel insights into the way people with PD become involved in dance, their views and opinions, and the suitability of our primary and secondary outcomes.

**Trial Registration:**

International Standard Randomized Controlled Trial Number (ISRCTN): 63088686; http://www.controlled-trials.com/ISRCTN63088686/63088686 (Archived by WebCite at http://www.webcitation.org/6QYyjehP7).

## Introduction

Parkinson disease (PD) is a common, progressive neurological condition estimated to affect 100-180/100,000 of the population [1]. People with this condition frequently experience deterioration of their spinal posture, mobility, and stability, leading to dependency and falls; therefore, preventing the cycle of inactivity and secondary complications is a priority. Despite disabling movement deficits, access to physiotherapy is limited [2]. Poor performance on measures of balance and functional tasks is common and has been associated with generalized deficits of attention and fall events, leading to decreased quality of life among sufferers [3]. The problem of unwanted secondary deterioration is of considerable concern.

People with PD experience slow movements (bradykinesia), rigidity, resting tremors, and abnormalities of postural reflexes. Gait characteristics include a shuffling pattern of walking with increased flexion of the hips and thoracic spine and reduced movement at the ankle with loss of heel strike. Restricted rotational movements of the head and trunk can contribute to the overall instability experienced by individuals. Key approaches to improving the function and activity of people with PD include balance and strengthening exercises [4] as well as strategies using rhythmical cueing to enable people to initiate movements [5]. Ballroom dancing comprises many of these facilitating components described; hence, the reason that dance was considered an appropriate activity for people with PD. The music provides the rhythmical cue for stimulating movement and the stepping and turning activities challenge balance control.

Self-help and physical leisure activities are increasingly important in the battle to maintain safe functional mobility among people with PD. Although there is growing evidence of the benefits of exercise for people with PD, research into the benefits of long-term exercises through leisure pursuits such as dance and self-help activities is limited. Research has shown that people with PD are interested in dance and early findings suggest a positive effect on balance and gait following Argentine tango classes, partnered or nonpartnered [6]. The effectiveness literature on dance in PD is growing, although the findings of the early studies have been limited by small sample sizes—the average study recruiting under 20 participants, and the largest recruited 52. These studies have shown proof of principle that dance, usually Argentine tango, for people with PD can be delivered [6-12] and can positively influence balance control and gait. Another study compared the tango with the waltz and the foxtrot and dance was superior to no dance but there was no distinction among dances. One-hour sessions, twice weekly for 10 weeks is beneficial. Only one recently completed study has evaluated dance delivered in the community. Earhart and Duncan [13] and Foster and Earhart [14] described a 12-month community-based tango program that demonstrated that dancing using community facilities was possible and they showed that those participants who danced increased their participation in activities of daily living. Positive effects were also shown when people were tested off medication.

Gaps in knowledge have been highlighted by a number of researchers. Two meta-analyses have identified the need for more well-designed randomized controlled trials and qualitative studies of the dance experience of people with PD [15,16]. Hackney and Earhart [6] highlighted a gap of knowledge concerning the long-term effects and cost effectiveness of dance. No existing studies have examined the influence of dance on spinal posture and turning (a task that inherently makes people unstable) or the personal insights of participants about their experiences with dance. We were aware that no-one had examined the feasibility of teaching a number of standard ballroom dances to people with PD through a local dance center in the UK or how a center would cope with finding dance partners for people with PD, and it is important to explore these feasibility issues before running a large multicenter trial.

Because this is a feasibility study, we will not be testing a hypothesis but will determine the methodological feasibility of evaluating the benefits of multiple dances taught through a dance center as a precursor to a definitive phase III trial. We need to understand how much dance people with PD and healthy partners will tolerate, which dances work best, how easy it is for dance teachers and dance centers to accommodate the needs of people with PD, and identify barriers and facilitators to participation in dance including the financial costs. We will build on the proof of principle studies [6-8] from the United States, address gaps in knowledge in planning a definitive trial of the impact of dance on balance and spinal posture, as well as turning, long-term follow up, economic evaluation, and user views. We will examine the appropriateness of primary and secondary outcomes currently envisaged for the future main trial and provide novel insight into user views on involvement in dance through a qualitative component, and develop procedures for economic evaluation for a future trial.

Specific questions of the feasibility study are:

1. What are the key routes to successful recruitment of healthy partners, people with PD, and dance centers to a randomized controlled trial of dance?

2. What are the most appropriate dances for people with PD?

3. How frequent, and how much dance is reasonable and likely to result in benefit for people with PD and healthy partners?

4. What specific adjustments do dance centers need to make regarding the delivery of dance to this group of people?

5. What level of dancing will be sustained to 3 and 6 months?

6. Will we obtain high quality data on spinal posture, balance, turning, and walking during home assessments?

7. Will we obtain high quality data on self-reported health status and balance confidence?

8. How appropriate and burdensome is the battery of assessments?

## Methods

### Overview

We followed the Standard Protocol Items: Recommendations for Interventional Trials (SPIRIT) guidelines [17] for developing the protocol and Figure 1 presents a diagrammatic representation of the study based on the Consolidated Standards of Reporting Trials (CONSORT) [18] flowchart. Two research fellows, physiotherapists with experience in PD, will conduct the research trial in collaboration with the dance teachers in a dance center in the South of England. Research fellow A will recruit participants and conduct baseline and follow-up assessments and will be blind to group allocation. Once a participant has consented to the trial, their name will be passed on to the second research fellow B, who will carry out the random allocation procedures, be present throughout all the dance classes, help arrange transport to the dance classes according to need, and organize volunteers for dance partners.

**Figure 1 figure1:**
[figure not shown]
Flowchart of trial design.

### Participants With Parkinson Disease

Research fellow A will obtain informed consent and recruit 50 people with PD from outpatient services, local support groups (Parkinson’s UK), and the DeNDRoN (Dementia and Neurodegenerative Disease Research Network, a clinical research network for dementia and neurodegenerative conditions). Eligible people with PD will have a confirmed diagnosis of PD, Hoehn and Yahr [19] scale of 1-3 indicating mild-to-moderate mobility and stability; will be able to stand, turn, and walk safely and unsupported but may experience freezing of gait [20]; will live at home; understand and follow commands, through a screen for cognitive impairment [21]; and be able to tolerate the dance intervention. People with PD lacking sufficient stability to dance with another person in the clinical opinion of research fellow A (eg, in danger of losing balance control each time they turn around) will be excluded. The decision as to whether a potential participant with limited mobility can safely undertake the dance intervention will be based primarily on their performance on the Berg balance scale (BBS) [22] and the motor component of the unified Parkinson’s disease rating score (UPDRS) [23]. For example, someone scoring 0 on questions 7, 8, or 13 of the BBS, indicating inability to “stand unsupported with feet together,” inability “to attempt to reach forward” in standing without losing balance or inability “to stand unsupported with one foot in front of the other” will be considered ineligible. The UPDRS motor component gait questions 29 and 30 will also be used as indicators: a severe disturbance of gait that requires constant assistance or lack of postural stability to such an extent that balance is spontaneously lost in standing, will also discount potential participants.

### Healthy Dance Partners

Healthy people identified by participants in the dance group will act as dance partners. Some people with PD will be single; others may have a spouse unwilling to participate, so relatives, volunteers, or responders to an advert will also be considered. The feasibility of recruiting healthy dance partners will be examined in the study. Our inclusion criteria for the dance partners are similar in age to people with PD, able to understand and follow commands, willing to participate, and able to tolerate the dance intervention. Evidence of a neurological condition, vestibular impairment, or multiple falls would lead to exclusion, but experience of a single fall would be acceptable (risk of falling is linked to repeated falling, not a single fall event) [24]. Otherwise healthy individuals who are considered to be at risk of instability while dancing will be excluded.

### Randomization

After the baseline assessment, eligible and consenting people with PD will be randomized to the dance or control group. Research fellow B obtained allocations by telephone from the trial medical statistician. Allocation will be randomized in 1 block of 11 participants (8 dance and 3 control), and 3 blocks of 13 (9 dance and 4 control), to yield participants entering each of 4 consecutive series of dance classes. The feasibility trial is too small to incorporate stratification. The dance-to-control ratio of 35:15 was chosen to maximize the number of people with PD experiencing the dance classes, while still including some control participants for feedback on the acceptability of randomization to control, retention, and fidelity in this group. The research fellow will contact participants to inform them of their allocation and of the times of their dance classes.

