### Qualitative Substudy

#### Aim

The aim of the qualitative substudy will be to identify and explore the views of people with PD and their dance partners about the appropriateness and acceptability of the dance programs and the perceived impact on their mobility. Their views of the trial procedures will also be explored. An experienced qualitative researcher has been employed to complete this part of the study.

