#### Methods

Fifteen of the 35 couples in the experimental group will be recruited to the qualitative study. Couples will be recruited with the aim of attaining maximum variation in the qualitative sample of the factors that may affect their experiences of the dance intervention, such as age, sex, and relationship with the dance partner.

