#### Interviews

In-depth, semistructured, qualitative interviews will be conducted using an interview guide developed for the study. The interviews will be conducted in the home separately with the people with PD and their dance partners where possible (where couples are spouses this may not be possible) within 1 month of completing the dance program. With participants’ consent, the interviews will be audiorecorded and fully transcribed. For people with PD, the interviews will explore the following issues: their perceptions of the impact of PD on their day-to-day lives and their experience of physiotherapy or any other interventions since diagnosis that were designed to promote activity; and experiences with exercise activity (dance or other exercise activity) before their diagnosis of PD. The following issues will be explored with people with PD and their dance partners: their reasons for deciding to take part in the dance program and their perceptions and expectations of it, the number of sessions they attended and reasons for missing any sessions or dropping out, what it was like to take part, enjoyment of the activity, maintaining enthusiasm for the activity, the implications of working with a partner, perceptions of the impact of participating in the dance program, interest in continuing with dance classes or other activity, and their perceived impact on their mobility. Participants will also be asked about any personal costs they experienced while participating.

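### Controls are included partly to learn how acceptable allocation to control is, but all 15 interview couples come from the dance arm

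*Protocol article*

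**What the plan says.** The Abstract (Methods) sets the design: "Fifty participants (mild-to-moderate condition) will be randomized to the control (usual care) or experimental (dance plus usual care) groups at a ratio of 15:35". The Randomization section gives the reasoning. "The dance-to-control ratio of 35:15 was chosen to maximize the number of people with PD experiencing the dance classes", and controls are kept "while still including some control participants for feedback on the acceptability of randomization to control, retention, and fidelity in this group". So the control arm has three stated purposes, and the first is what controls think of having been allocated to control.

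The Qualitative Substudy describes the interviews. Its Aim covers "the views of people with PD and their dance partners about the appropriateness and acceptability of the dance programs", and adds: "Their views of the trial procedures will also be explored". Its Methods fix the sample: "Fifteen of the 35 couples in the experimental group will be recruited to the qualitative study". Its Interviews section times them "within 1 month of completing the dance program" and lists topics that mostly concern the dance program. The Abstract also says that the qualitative work will look at general trial procedures.

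Two other parts of the article bear on controls. Under Assessments, participants in either arm receive a questionnaire at the final assessment, to be completed in their own time and posted back. It covers resource use and views on the acceptability and benefits of the project. Under Statistical Analysis, feasibility is addressed by counting those who are recruited and who complete each part of the protocol.

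**The concern.** People who agree to a dance trial and are then told to carry on as usual are the ones best placed to say whether that allocation was tolerable, whether it made them think of leaving, and what would have kept them in. A feasibility study needs this before a definitive trial is designed, and the article names it as a reason for having controls. Yet the most searching method in the study, the in-depth interview, is reserved for the other arm by a sampling rule that the article itself fixes. This is therefore not a detail left to a fuller document.

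The article treats control follow-up as something that needs support, since the Control Group section offers dance vouchers to encourage it. If some controls do withdraw, the study will have the number but no planned way to learn their reasons. The main trial would then choose its control condition, its consent wording and its retention measures with less information than this study could have supplied at almost no extra cost.

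**Working it through.** **Inputs.** Block structure and arm sizes: Randomization section. Interview sample: Qualitative Substudy, Methods. Separate or joint interviews: Qualitative Substudy, Interviews.

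**Step 1: reproduce the arm sizes.** The blocks are "1 block of 11 participants (8 dance and 3 control), and 3 blocks of 13 (9 dance and 4 control").
- Dance: 8 + 3 × 9 = 35.
- Control: 3 + 3 × 4 = 15.
- Total: 35 + 15 = 50. All three agree with the stated figures. Controls are 15/50 = 30% of the sample.

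**Step 2: interview coverage by arm.**
- Dance: 15/35 = 42.9% of couples.
- Control: 0/15 = 0%.

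**Step 3: which source can answer which question about controls.**
- Interviews: none planned with controls, and the timing rule cannot apply to someone with no dance program to complete.
- Final questionnaire: open to controls. It is handed out at the final assessment, so as described it misses those who have already left. It is described as asking about the project in general; allocation to control is not named.
- Completion counts: include controls who withdraw, and so address retention, but carry no reasons.
- Anonymous questionnaire for people who decline (Qualitative Substudy, Analysis): concerns people who were never randomized.

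The documents give no return rate for the final questionnaire. If 70% to 90% of 15 controls returned it (assumption), that would be 0.70 × 15 = 10.5 to 0.90 × 15 = 13.5, or about 10 to 13 replies, fewer if some have withdrawn.

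**Step 4: what the interview budget allows.** Partners are interviewed separately where possible, which may not be possible for spouses. A couple is therefore 1 or 2 interviews.
- Planned: 15 × 1 = 15 to 15 × 2 = 30 interviews.
- Two couples released: 2 × 1 = 2 to 2 × 2 = 4 interviews.
- Dance coverage afterwards: 13/35 = 37.1% of couples, against 42.9%.
- Control coverage afterwards: 2/15 = 13.3% to 4/15 = 26.7%, against 0%.

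**Step 5: what so few control interviews can show.** If a view is held by a share p of controls and m are interviewed as if at random (assumption), the chance of hearing it at least once is 1 − (1 − p)^m.
- p = 0.2, m = 2: 1 − 0.8² = 0.36.
- p = 0.2, m = 4: 1 − 0.8⁴ = 0.59.
- p = 0.2, all 15 asked and answering: 1 − 0.8¹⁵ = 0.965.

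A handful of interviews gives depth but would often miss a minority view. A direct question in the questionnaire gives breadth but little depth, and misses those who withdrew. Each covers the other's weakness, which is why both belong in the remedy.

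**The case against.** The strongest reply is that nothing in the article is contradicted. The Randomization section promises feedback, not interviews. The substudy's aim is mainly the dance program, and none of the eight specific questions in the Introduction names the acceptability of being a control. Which method serves which question is a design choice. This stands in part: the point is a mismatch of purpose and method, not an error.

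A second reply is that controls are covered by other means. A reader might infer from the interview sample that trial procedures will be judged only by the dance arm, or that controls' views go uncollected. The documents do not support that. The final questionnaire is not restricted by arm, retention is counted in both arms, and physical activity is recorded at baseline, 3 and 6 months through the phone-FITT, again without restriction by arm. Nor is the questionnaire the whole evidence on controls. What these sources do not provide is an account in depth, or any account from controls who leave before the final assessment. The exact questionnaire items may well be in the full protocol, so the absence of a direct question is a point to confirm rather than a proven gap.

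A reader might also infer that the interview sample shuts out dancers who dropped out. That does not hold either. The sampling factors are given only as examples, the interview topics include reasons for missing sessions or dropping out, and the timing rule can be read as the end of the 10-week program.

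**Conclusion.** The point holds as a cheap improvement. Controls are included partly to report on the acceptability of their allocation, and 0 of the 15 will be interviewed, against 15 of 35 dance couples. The only described source of controls' own views is a general take-home questionnaire at the final assessment, which, as described, does not reach those who withdraw earlier. The completion counts add numbers without reasons.

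This rests on the article's own sampling rule and on no numerical assumption. The assumed return rate and the detection probabilities only indicate scale.

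It would be tempting to go on to say that acceptability will be biased upward because only people who received dance are interviewed. That may be a reasonable suspicion, but nothing in the documents establishes its direction or size, and controls' questionnaire replies also contribute. It is not part of this conclusion.

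**What to change.** - In Qualitative Substudy, Methods, replace about 2 of the 15 dance couples with 2 to 4 control participants. The number depends on whether the released couples would have been interviewed separately. Give priority to any control who withdraws and agrees to be interviewed.
- In Interviews, set the timing for controls: after the 6-month assessment, or at withdrawal. For those who stay in the trial, this leaves the blinded assessments untouched. Add a short topic guide on how allocation to control was received, whether it affected staying in the trial, and what other activity was taken up.
- In Aim, extend the sentence on trial procedures to people allocated to control.
- In Assessments, state that the final questionnaire asks controls explicitly about being randomized to control.

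The cost is about 13 instead of 15 dance couples (37.1% instead of 42.9% of the arm), changes to the protocol and topic guide, and an ethics notification. The number of interviews stays within the planned budget if the count of control interviews is matched to what the two released couples would have used.
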